### Outcomes

The primary outcome is the success rate of the treatment protocol, defined as no requirement for further treatment until complete resolution of the CSP as demonstrated by negative beta hCG levels and absence of residual gestational material on ultrasound examination. Treatment failure is defined as the need for further treatment before complete resolution of the CSP. Secondary outcomes are use of additional procedures, intra- and postoperative complications, blood transfusions, admission to intensive care unit (ICU), maternal death and length of stay (LOS) in the hospital.

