### Sample size calculation

The sample size calculation was based on detecting an effect that produces an increase in the primary outcome from a baseline successful rate of 65% (women undergoing D&E) (Kanat-Pektas et al., 2016) to a success rate of 95% (women undergoing hysteroscopy surgery) (Ash et al., 2007; Deans and Abbott, 2010; Birch Petersen et al., 2016). Given an alfa of 0.05 and 80% power, a sample size of 54 women is planned (27 for each intervention group).

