### Statistical analysis

Univariate comparisons of dichotomous data will be performed with the use of the chi-square test with continuity correction. Comparisons between groups will be performed with the use of the T-test to test group means by assuming equal within- group variances.

The primary analysis will be an intention to treat comparison of the treatment assigned at randomization. The effect of hysteroscopic resection on the cumulative incidence of each outcome will be quantified as the relative risk (RR) and its 95% confidence interval (CI). A 2-sided P value less than .05 was considered significant.

Statistical analysis was performed using Statistical Package for Social Sciences (SPSS) v. 19.0 (IBM Inc).

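### The continuity-corrected test and the relative-risk interval can give opposite answers on the primary outcome in about one trial in ten, and the relative risk has no usable interval for the rarest safety outcomes (low severity)

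*Protocol article*

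**What the plan says.** Under Statistical analysis, the protocol article makes two commitments for dichotomous outcomes. The test is the "chi-square test with continuity correction". The effect measure is the relative risk with its 95% confidence interval: "The effect of hysteroscopic resection on the cumulative incidence of each outcome will be quantified as the relative risk (RR". The significance rule is "A 2-sided P value less than .05 was considered significant". No method is named for the interval, and no other effect measure is named for incidence outcomes.

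Under Outcomes, the primary outcome is treatment success. The secondary outcomes include "blood transfusions, admission to intensive care unit (ICU), maternal death and length of stay (LOS) in the hospital". No event rates are given for them. Length of stay is continuous and falls under the t-test sentence, not under the relative risk.

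The Sample size calculation section goes from "a baseline successful rate of 65% (women undergoing D&E" "to a success rate of 95% (women undergoing hysteroscopy surgery". It then states: "Given an alfa of 0.05 and 80% power, a sample size of 54 women is planned", that is, 27 per arm.

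**The concern.** There are two separate problems.

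- **Primary outcome.** The continuity correction makes the test conservative, while the usual log-scale interval for a relative risk carries no such correction. In borderline tables the interval can exclude 1 while the p-value is above 0.05. The p-value is the stated rule, so the trial would formally be negative while its printed interval says otherwise.
- **Rare safety outcomes.** When one arm has no events, the relative risk is zero or infinite. When both arms have none, it is undefined. The usual interval does not exist in any of these cases. If nothing else is shown, an empty entry for death or ICU admission may be read as no risk, although 27 women cannot show that.

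**Working it through.** **Inputs.** Success 95% versus 65%, 27 per arm, 80% power and alpha 0.05 come from Sample size calculation. The two-sided rule, the corrected chi-square and the relative risk with 95% interval come from Statistical analysis. Two things are assumed: the interval is the log-scale (Wald) one, and the safety event rates are as listed in step 4.

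**1. The plan's own figure.** Pooled-variance formula without continuity correction, mean rate 0.80:

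n = [1.96·√(2·0.80·0.20) + 0.8416·√(0.65·0.35 + 0.95·0.05)]² / 0.30² = (1.1087 + 0.4413)² / 0.09 = 26.7, so 27 per arm.

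The stated 54 is reproduced, but only without the correction. With it, the same formula needs 34 per arm.

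**2. One borderline table: 26/27 versus 20/27** (failures 1 and 7).

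- Corrected chi-square: |26·7 − 20·1| − 27 = 135. Then 54·135² / (27·27·46·8) = 3.67, p = 0.055.
- Uncorrected chi-square: 54·162² / (27·27·46·8) = 5.28, p = 0.022.
- Relative risk: (26/27)/(20/27) = 1.30. SE(log) = √(1/26 − 1/27 + 1/20 − 1/27) = 0.1199. Interval: exp(0.2624 ± 1.96·0.1199) = 1.03 to 1.64.

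The planned test is not significant, yet the interval excludes 1. A second example is 27/27 versus 22/27: p = 0.060, relative risk 1.23 with lower limit 1.02.

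**3. How often.** All 28 × 28 possible tables were enumerated with binomial weights. At 95% versus 65%:

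| Result | Share of trials |
|---|---|
| Corrected p < 0.05 | 71.5% |
| Log-scale interval for the relative risk of success excludes 1 | 81.9% |
| The two disagree | 10.4% |

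Disagreement always runs the same way: the interval excludes 1 and p is at least 0.05 (81.9 − 71.5 = 10.4). At 95% versus 75% it is 16.2%. With equal rates of 65%, 80% and 95% it is 1.6%, 2.2% and 2.1%.

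To locate the cause, vary one element at a time, at 95% versus 65%:

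| Interval | Disagrees with corrected test | Disagrees with uncorrected test |
|---|---|---|
| Relative risk, log scale | 10.4% | 4.0% |
| Risk difference, Newcombe | 10.0% | 4.3% |
| Risk difference, Miettinen-Nurminen | not computed | 1.7% |

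Changing the effect measure hardly helps. Dropping the correction does.

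Operating characteristics with 27 per arm:

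| Test | Exact power | Largest exact type I error |
|---|---|---|
| Corrected chi-square (planned) | 71.5% | 2.6% |
| Uncorrected chi-square | 85.9% | 5.7% |
| Boschloo unconditional exact | 81.5% | 4.5% |

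**4. Empty arms.** For a common event rate p, one arm of 27 is empty with probability q = (1 − p)²⁷. At least one arm is empty with probability 1 − (1 − q)², and both with q².

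| Assumed rate | At least one arm empty | Both arms empty |
|---|---|---|
| 0.1% | 99.9% | 95% |
| 1% | 94% | 58% |
| 2% | 82% | 34% |
| 5% | 44% | 6% |
| 10% | 11% | 0.3% |

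Zero events in 27 women still leaves an exact two-sided 95% upper limit of 1 − 0.025^(1/27) = 12.8%.

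**The case against.** The strongest case against is that a relative risk with a 95% interval is a standard measure. An article commonly leaves the interval method, a zero-cell rule and supplementary measures to an analysis plan that is not shown. That stands: their absence is not a finding here. What remains is that two methods are stated and fit each other, and this sample size, poorly.

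Several stronger readings are tempting, but the documents do not support them.

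- **That every outcome is reported by the relative risk alone.** The text does not exclude other measures or counts per arm, and length of stay goes to a t-test.
- **That the trial expects zero events.** No rates are given for transfusion, ICU admission or death. The Discussion speaks of high maternal morbidity, so transfusion need not be rare. At 10% an empty arm occurs in only 11% of trials.
- **That the primary outcome suffers from empty cells.** It is defined and powered as success, and an arm without successes is practically impossible. The chance of no failure in the hysteroscopy arm, 0.95²⁷ = 25%, matters only if the relative risk of failure were reported, which no section says.
- **That the relative risk causes the conflict with the p-value.** A Newcombe risk difference conflicts with the planned test almost as often (10.0% against 10.4%).

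Dropping the correction also has a price: exact type I error reaches 5.7% at a common rate of 80%, where the planned test has 1.9%.

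**Conclusion.** The point holds in a limited form. At the design rates and 27 analysed women per arm, the planned test and a log-scale relative-risk interval contradict each other on the primary outcome in 10.4% of trials, mainly because of the continuity correction. That figure rests on the assumed interval method. The drop in exact power to 71.5% does not; it follows from the stated test and the design rates. The mismatch between the sample size formula and the planned test is a related but separate issue.

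For incidence outcomes, the one named effect measure will probably not be estimable for very rare events such as death, and possibly ICU admission. How often depends entirely on the assumed rates. Severity is low: this concerns the match of test and interval, and reporting. The choice of the relative risk is not itself an error.

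**What to change.** **Primary outcome.** Either of these would do:

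- Replace the corrected chi-square with an unconditional exact test such as Boschloo's, and report a confidence interval obtained by inverting the same statistic.
- Use the uncorrected score test with its matching score interval, and state that exact type I error can reach 5.7%.

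Do not pair either test with a Newcombe interval and claim agreement. A Miettinen-Nurminen interval beside the uncorrected chi-square still disagrees in 1.7% of trials, because it carries an extra N/(N − 1) variance factor. The matched interval should therefore be the one used to interpret the primary result.

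**All dichotomous outcomes.** Give counts per arm, and the risk difference with a score-type (Miettinen-Nurminen) 95% interval beside the relative risk. The risk difference is finite in every table, including when both arms are empty. For an arm with no events, give the exact upper limit (12.8% for 0/27).

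**Cost.** A few sentences of analysis text, minor programming and an extra table column. Changing the primary test is more than a wording change and should be fixed before the outcome data are seen. Whether the named SPSS version offers the exact test and interval should be checked. No change to recruitment or conduct is needed.

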## Discussion

CSP is a rare form of ectopic pregnancy with the incidence raising globally. CSP is associated with high risk of maternal morbidity and potential mortality. Recently, a review by Birch Petersen et al. (2016) evaluated treatment modalities for CSP, focusing on efficacy and complications. They found limited data on the superiority of any intervention over others, with recommendations primarily based on case series and retrospective studies.

Only 4 randomised trials (Peng et al. 2015; Zhuang and Huang 2009; Qian et al. 2015; Li et al. 2011) evaluating treatment of CSP have been published so far. All of them were performed in China. Zhuang and Huang (2009) compared uterine artery embolisation (UAE) with systemic MTX (sample size 72 patients). Li et al. (2011) compared systemic MTX with transcatheter arterial chemoembolisation using different embolic agents (sample size 26 patients). Peng et al. (2015) compared local with systemic MTX (sample size 104 patients). Finally, Qian et al. (2015) compared D&C with operative hysteroscopy in combination with preventive UAE (sample size 66 patients). Notably, UAE appears as a technique associated with a high risk of major complications (Kröncke and David 2019).

To the best of our knowledge, this is the first randomised trial comparing the success rates of hysteroscopic resection with D&E for treatment of CSP following MTX treatment. We anticipate that hysteroscopic surgery has beneficial effects on treatment of CSP compared to D&E. The results of the trial will provide information on the best treatment for CSP.
